### Recruitment

Patients presenting to the clinic will first be booked for THA by their surgeon. The surgeon will then assess whether the patient is eligible for possible outpatient discharge and will broadly discuss the study with the patient. The surgeon will then ask if the patient is interested in hearing more about the study and whether the research assistant may contact them with further information. Once patient approval is received, the patient is contacted by the research assistant with more information. All patients will be given the necessary time to consider their participation in the study and to provide informed consent if willing to participate.

### Randomization

#### Concealment mechanism/implementation

Potential participants will be initially screened by their treating surgeon and approached for participation by the research assistant. To reduce selection bias, patients are randomized into group using a stratified and blocked scheme after eligibility has been fully determined. The research assistant will confirm their eligibility and, after obtaining consent, will enter the patient’s date of birth and whether they’ve had previous experience with THA before randomizing the patient via a web-based randomization system to inpatient or outpatient.

#### Allocation (sequence generation)

All participants will be randomized by the research assistant using a 1:1 ratio for inpatient to outpatient. Randomization will be stratified by surgeon and previous experience with THA (had a THA on the contralateral limb or were the caregiver for someone whom had a THA). All patients will be analyzed according to the treatment group as assigned regardless of when they were discharged.

#### Blinding

To reduce detection bias, patients will be unaware that they were randomly assigned to a discharge plan and remain blinded to the presence of a comparison group until they reach the end of the study. Participants are kept blinded to group allocation using a modified Zelen consent model [19]. In this design, eligible patients are randomized to the intervention prior to providing consent to minimize the risk of bias associated with knowledge of the alternative intervention. We posit that patients with a bias for inpatient care who are randomized to the outpatient group may be more likely to return to seek additional care significantly biasing costs. Alternatively, patients with a strong preference for outpatient care who are randomized to the inpatient group may bias measures of satisfaction. Thus, patients are asked to consent to participation in a research study evaluating the outcomes and costs associated with patients undergoing THA; they are not told about randomization, the existence of an alternative group, or the between-groups objectives. At the end of the study, all patients are informed about the deception and asked to consent to having their data used for analysis.

As data collection occurs on the day of discharge from the hospital, it is not possible to blind the research assistant responsible for collecting patient-reported outcomes, however since outcomes are patient-reported, we do not expect an increase in the risk of detection bias. We are also unable to blind investigators to group allocation.

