#### Secondary outcomes

Our secondary outcomes include patient-reported satisfaction, health-related quality of life (HRQOL), function, pain, and caregiver assistance. Patients will be asked to rate satisfaction with pain control, safety and quality of care on either a 100-mm visual analogue scale (VAS) with a score of 100 representing the highest possible satisfaction, or on a five to seven-point ordinal scale (completely satisfied to completely unsatisfied).

We will measure HRQOL using the *Western Ontario and McMaster Universities Osteoarthritis Index* (WOMAC), which includes three arthritis-specific domains of pain, stiffness and physical function. It has demonstrated content, cross-sectional and construct validity, good internal consistency reliability and moderate to high test retest reliability in patients undergoing THA and TKA [13]. To measure function, we will use the *Harris Hip Score* (HHS) [14]; a valid and reliable objective functional measure completed by the surgeon. We will measure general health using the *12-Item Short Form Health Survey* (SF-12v2) and th*e European Quality of Life Scale* (EQ-5D). The SF-12 evaluates limitations on physical and social activities, activities of daily living, pain, mental health and well-being, and perceptions of health and is valid, reliable, and responsive in patients with arthritis [15]. The EQ-5D index includes domains of mobility, self-care, usual activities, pain, anxiety and depression and has good test retest reliability and cross-sectional construct validity in patients with arthritis [16]. We will measure pain using a self-administered *Numeric Pain Rating Scale* (Pain NRS), ranging from 0 (no pain) to 10 (worst). We will measure the level of assistance provided by the caregiver throughout the recovery period using the *Caregiver Assistance Scale* (CAS) [17] and *Caregiver Strain Index* (CSI) [18].

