### Plan for statistical analysis

We will present the incidence of serious adverse events by group at 30 days postoperative and calculate a risk difference and relative risk with 95% confidence intervals around the estimates. The mean and standard deviation for all continuous outcomes (Satisfaction, WOMAC, SF-12, HHS, Pain NRS, and CAS) will be calculated for each group at each time point and calculate the mean between-group difference with 95% confidence interval. Linear mixed models, using a covariance structure that allows for correlations between measurements to decline as they are further apart in time will be used to evaluate improvements in function after surgery since this provides a powerful approach to analyze complex longitudinal data while controlling for important covariates such as gender, comorbidities, age and surgeon/site. All data will be analyzed according to the intention-to-treat principle with an as treated analysis also performed.

We will conduct a cost-effectiveness analysis from both a Canadian healthcare payer and societal perspective using the incidence of adverse events as our effectiveness outcome to estimate cost-effectiveness at 3 months postoperative. We will determine cost-effectiveness using the net benefit regression (NBR) framework to estimate the incremental net benefit (INB) of outpatient arthroplasty [22]. An intervention is considered to be cost-effective if the INB is greater than zero. NBR also provides a means to adjust for potentially confounding factors and therefore allows greater statistical efficiency and a more precise estimate of the INB. To characterize the statistical uncertainty around our estimate of INB we will calculate 95% confidence intervals, and a cost-effectiveness acceptability curve [23].

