### Data collection methods

Follow-up assessments for this study coincide with the standard of care follow-up schedule for the surgeons at our centre. During each visit, the research assistant will administer the questionnaires to the participants and ensure they are completed. Alternatively, participants are also given the option to complete questionnaires online by directly accessing the electronic data capture (EDC) system (*Empower Health Research*). The HHS will be completed by the treating surgeon at the three-month visit.

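### The patient-reported rationale for unblinded data collection does not cover the Harris Hip Score, which the treating surgeon completes

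*Protocol article*

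**What the plan says.** Under Blinding, the article explains that "it is not possible to blind the research assistant responsible for collecting patient-reported outcomes", and continues that "since outcomes are patient-reported, we do not expect an increase in the risk of detection bias". The next sentence adds: "We are also unable to blind investigators to group allocation". No safeguard for investigator-scored outcomes follows.

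Under Secondary outcomes, the sentence beginning "To measure function, we will use the" names the Harris Hip Score and describes it as "a valid and reliable objective functional measure completed by the surgeon". Data collection methods repeats this for follow-up: "The HHS will be completed by the treating surgeon at the three-month visit".

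The HHS enters the between-group analysis. The Plan for statistical analysis states: "The mean and standard deviation for all continuous outcomes (Satisfaction, WOMAC, SF-12, HHS, Pain NRS, and CAS) will be calculated for each group", followed by mean differences with 95% confidence intervals. The same section says that linear mixed models "will be used to evaluate improvements in function after surgery", without naming the instrument.

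**The concern.** The only reason given for expecting no added detection bias is that the patient supplies the answer. For the HHS the surgeon supplies it. The patient-side blinding from the modified Zelen consent cannot protect a score that is given by someone else who knows the allocation. Describing the HHS as objective may also lead readers to trust it more than the questionnaires, although it is the secondary instrument most exposed to the rater's knowledge.

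At stake is the secondary comparison of function. If surgeons score their same-day patients a little differently from their overnight patients, the HHS could show a difference that does not exist or hide one that does.

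**Working it through.** **Step 1: who scores what, and who is blinded.**

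- Patients: unaware of randomization and of the other arm until the end of the study (Blinding).
- Research assistant: not blinded, and collects the patient-reported outcomes (Blinding).
- Investigators: not blinded (Blinding).
- HHS: completed by the surgeon (Secondary outcomes), specifically the treating surgeon at 3 months (Data collection methods).
- WOMAC, including a physical function domain: listed among the health-related quality-of-life measures (Secondary outcomes). The article does not assign it to the surgeon. Questionnaires are administered to participants, on paper or online (Data collection methods).

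That the treating surgeon knows the arm is an inference, because the article says investigators and not treating surgeons. It is a strong inference: surgeons screen and operate on these patients, the arm determines the day of discharge, and no blinding of surgeons is described.

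**Step 2: does the design remove the problem?** Randomization is stratified by surgeon, and surgeon/site is a model covariate. If a surgeon scores everyone high or low, that tendency falls on both arms and largely cancels. If a surgeon scores one arm higher than the other, the difference goes straight into the treatment contrast, and neither stratification nor adjustment removes it.

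**Step 3: is there a less exposed measure at the same times?** Table 2 schedules HHS and WOMAC at the same two visits, baseline and 3 months. No new data would be needed.

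**Step 4: illustration of scale.** The number per arm comes from the sample-size section. With 8% risk in both arms, a 6-point margin, one-sided 5% and 80% power:

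n per arm = (1.645 + 0.842)² × 2 × 0.08 × 0.92 / 0.06² = 252.8, so 253 per arm and 506 in total.

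This reproduces the article's 506. The present point does not alter that figure; 253 is only used as the arm size below.

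The article gives no SD for the HHS and no size for any scoring lean. I assume SDs of 10, 15 and 20 points, leans b of 1 and 2 points that differ by arm, no true difference, and no loss by 3 months.

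SE = SD × √(2/253)

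Chance that the two-sided 95% interval excludes zero = Φ(−1.96 + b/SE) + Φ(−1.96 − b/SE)

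| Assumed SD | SE | b = 1 point | b = 2 points |
|---|---|---|---|
| 10 | 0.889 | 20.3% | 61.4% |
| 15 | 1.334 | 11.6% | 32.3% |
| 20 | 1.778 | 8.7% | 20.3% |

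With no lean the figure is 5%. A sample sized for an uncommon binary event gives a narrow interval on a continuous score, so a small differential lean can look like an effect. The table does not show that such a lean exists.

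**The case against.** The strongest defence is that the sentence is narrower than it looks. Its subject is the research assistant who collects patient-reported outcomes, and it says only that no increase in bias is expected. A reader might infer that the protocol rules out detection bias altogether. It does not, and the following sentence discloses that investigators are unblinded. This stands, but on the narrow reading the surgeon-scored HHS has no rationale or safeguard at all.

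A reader might also infer that the planned function model depends on the HHS, or that function is the only outcome with a named model. Neither is supported. Net benefit regression is named for cost-effectiveness. The mixed model is tied to no instrument, and its covariance structure, with correlation declining over time, has nothing to act on when there are only two time points. The HHS has just two, as does WOMAC. What remains is the planned HHS mean difference with its confidence interval, which is enough for the point.

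The objection that the percentages come from assumed inputs is correct. The article also states no significance rule for secondary outcomes, so the figures serve only as illustration.

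Finally, ranking secondary outcomes is often left to the SAP, which is not shown. The lack of a ranking is not the fault raised here. The fault is a stated rationale that does not fit the article's own outcome list.

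**Conclusion.** The point holds for one secondary outcome. The reason given for expecting no added detection bias does not apply to the HHS, which the article names as its measure of function and has the surgeon complete. The bias is possible, not demonstrated, and its direction and size are unknown. The conclusion rests on the inference that treating surgeons know the arm, and on a lean that differs by arm and not a constant scoring habit.

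A reader might take this to undermine the trial's main results. The documents do not support that. The stated objectives are serious adverse events and cost-effectiveness, and the economic analysis uses adverse events as its effect measure. The HHS enters neither.

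**What to change.** Three changes of wording:

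1. In Blinding, limit the statement about detection bias to the patient-reported instruments.
2. In the same place, state that the HHS is scored by a surgeon who is not blinded to allocation.
3. In the Plan for statistical analysis, or in the SAP, say that the between-group conclusion on function rests on patient-reported WOMAC physical function at 3 months, with the HHS reported as supportive.

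Both instruments are already collected at baseline and 3 months, so no staff, visits or patients are added. The small downside is that the HHS result carries less weight. WOMAC is not fully protected, since an unblinded research assistant administers the questionnaires, but the patient gives the answers without knowing of a comparison group.

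The way the HHS is completed should stay as it is. Recruitment was ongoing when the article was written, and moving some items to patient completion would mix two modes of administration within the trial.

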### Sample size

A retrospective analysis of over 50,000 THA and TKA procedures found no differences in 30-day major complications or readmissions among patients with a zero to two-day hospital stay compared to those discharged on day three or four postoperative [4]. The rate of serious adverse events in the inpatient group is expected to be greater than 5 % [20]. To define a non-inferiority margin we agreed that no more than a 5 % increase in the risk of serious adverse event (risk difference ≥ 6% favouring inpatient care) was acceptable. If the risk in the inpatient group ranges between five to 8 % and there is truly no difference in risk of serious adverse event between the groups, then a maximum of 506 patients are required to be 80% certain that the upper limit of a one-sided 95% confidence interval will exclude a difference in favour of the inpatient group of more than 6 % [21]. Given that the primary outcome is being measured at 30-days postoperative, we anticipate a low lost-to-follow-up rate. Previous studies conducted at the lead study site in similar patients demonstrate loss to follow up rates less than 1 % for the first 30 days. Therefore, to account for a potential 1 % dropout rate we inflated our sample size to 511.

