## Discussion

This protocol is for a multi-centered randomized controlled trial to assess the safety and cost-effectiveness of outpatient total hip arthroplasty compared to standard inpatient care. There is currently a lack of high-quality studies evaluating the safety and effectiveness of outpatient THA. Most studies that have assessed safety have used US national databases [24–29] or observational cohort designs [30–33] with only one published randomized trial [34]. Previous prospective studies have also been underpowered to detect differences in complication rates between outpatient and inpatient care groups. Due to the already low rates of serious adverse events after THA, reported from 3.8% up to 8.6% in the literature, [20, 35, 36] sample sizes must be sufficiently large to include a sufficient number of events to support clinical conclusions. Our protocol will be the first adequately powered prospective study to evaluate the safety of outpatient THA.

One strength of our study protocol is the use of a modified Zelen consent model [19], as one of the difficulties with assessing outpatient discharge in comparison with standard inpatient care is potential patient biases. This design allows us to avoid these biases as patients with a strong preference for either group are not made aware of the alternative intervention. A weakness of the randomized trial by Goyal et al. (2017) was the lack of blinding which led to a significant number of crossovers due to personal preference [34]. Our use of a modified Zelen consent model [19] should help to address this issue and reduce the number of crossovers in our study. Future studies looking to evaluate outpatient THA should also consider use of this design to strengthen their conclusions and reduce patient crossover.

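### The non-inferiority margin is worded as both 5% and 6% in one sentence; the sample size uses 6 points, and a result between the two has no defined verdict

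*Protocol article*

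**What the plan says.** The margin appears only in the protocol article's Sample size section. The defining sentence says that the investigators agreed that "no more than a 5 % increase in the risk of serious adverse event (risk difference ≥ 6% favouring inpatient care) was acceptable". It first puts the limit at 5%, and then, in a bracket meant to express the same limit, at 6%. The sentence after it sets the criterion: "the upper limit of a one-sided 95% confidence interval" "will exclude a difference in favour of the inpatient group of more than 6" percent. Under that criterion, with an inpatient risk of 5 to 8% and no true difference, "a maximum of 506 patients are required to be 80% certain". The figure is then raised to 511 for 1% dropout.

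The section on the plan for statistical analysis promises a risk difference and a relative risk with 95% confidence intervals. It does not repeat a margin, so nothing elsewhere in the article settles which figure governs.

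**The concern.** In a non-inferiority trial the margin is the decision rule. Here the primary outcome is serious adverse events within 30 days, so the margin decides whether same-day discharge is declared acceptably safe. A limit of 5 points and a limit of 6 points are different rules. Taken literally, the bracket even places differences of 6% or more on the acceptable side.

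Two things are at stake. First, a result whose upper limit falls between 5 and 6 points could be reported as non-inferior or as not non-inferior, with the protocol cited in support of either. Second, the 80% power claim belongs to 6 points. If the clinical agreement was 5 points, the claim does not hold over the whole risk range for which it is made.

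**Working it through.** **Inputs** (Sample size section, except allocation, which is from Allocation under Randomization): one-sided level 0.05; power 80%; true difference 0; inpatient risk p between 5% and 8%; 1:1 allocation; margin d of 6 or 5 percentage points. The 5% is read as absolute, because the bracket beside it is a risk difference.

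**Formulas.** Per arm, n = 2p(1−p)(1.645 + 0.842)² / d², where the squared sum is 6.1826 from unrounded normal quantiles. Power with 253 per arm is Φ(d/SE − 1.645), with SE = √(2p(1−p)/253).

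**Reproducing the plan's figure.** At p = 0.08 and d = 0.06: n = 2 × 0.08 × 0.92 × 6.1826 / 0.0036 = 252.8, so 253 per arm and 506 in total. SE = √(0.1472/253) = 0.02412, and power = Φ(0.06/0.02412 − 1.645) = 80.0%. For dropout, 506/0.99 = 511.1, which agrees with 511. The trial was sized on 6 points at the top of the stated risk range.

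**Same calculation with 5 points.** At p = 0.08: n = 0.1472 × 6.1826 / 0.0025 = 364.03, so 365 per arm and 730 in total. With 253 per arm, power = Φ(0.05/0.02412 − 1.645) = Φ(0.428) = 66.6%.

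**Over the stated range:**

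| Risk in both arms | Power with 506, 6 points | Power with 506, 5 points | Total for 80% power, 5 points |
|---|---|---|---|
| 5% | 92.7% | 82.5% | 470 |
| 6% | 88.4% | 76.5% | 558 |
| 7% | 84.1% | 71.2% | 644 |
| 8% | 80.0% | 66.6% | 730 |

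**Sensitivity to method.** Exact binomial power of the one-sided 95% Wald limit, with 253 per arm and 8% risk, is 80.1% for 6 points and 67.4% for 5. With the Farrington-Manning restricted variance, 5 points at 8% risk needs 760 patients, and 506 give 64.6% power. The choice of method does not close the gap.

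**How often the verdict would depend on the wording.** Take 20 inpatient events among 253 (7.91%). With 23 outpatient events among 253 (9.09%), the difference is 1.19 points, the standard error 2.479 points, and the upper limit 1.19 + 1.645 × 2.479 = 5.26 points. With 24 outpatient events it is 5.70 points. Both results pass at 6 and fail at 5. The exact probability that the upper limit falls between the two margins is the difference of the exact powers: 80.1% − 67.4% = 12.7% at 8% risk, and 92.3% − 82.2% = about 10% at 5% risk, if the arms truly do not differ.

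**The case against.** The best defence is that the operative margin can be identified. The only sentence that sets a confidence-limit criterion uses 6%, and both 506 and 511 follow from it. The bracket can be read as naming the unacceptable side in whole percentages: up to 5% is tolerable, 6% or more is not. On that reading the two numbers are one threshold, badly worded, and it is hard to believe that anyone meant a difference of 6% or more to be acceptable. This stands as an account of the likely intent, and it shows that 506 is not a calculation error. It does not settle the rule, because a risk difference is continuous and the whole-percentage reading says nothing about 5.26 or 5.70 points.

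It is also fair that 67% is the worst case. The plan gives a range of risks and not one planning value, and at 5% risk 506 patients still give 82.5% power for a 5-point margin.

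A reader might further infer that 506 is wrongly called a maximum, since the Discussion cites rates "reported from 3.8% up to 8.6% in the literature", and at 8.6% with 6 points 540 patients would be needed (506 give 77.7%). The document does not support that as an error. The statement is conditional on a risk of 5 to 8%, and within that condition 506 is the maximum. The Discussion range is background literature, and planning on a narrower range is legitimate.

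**Conclusion.** The point holds as an internal contradiction in the primary decision threshold. The sample size is correct for 6 points; the protocol does not make clear that 6 points is what was agreed as acceptable. If it was 5, power with 506 patients runs from 82.5% at 5% risk down to 66.6% at 8%, and 80% is not held across the stated range. If the arms truly do not differ, roughly one trial in ten (5% risk) to one in eight (8% risk) would end with an upper limit in the disputed interval.

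A reader might conclude that the trial is underpowered at 67%, or that no margin other than 6 can go with 506. Neither follows: the first requires both a 5-point margin and an 8% risk, and the second fails at 5% risk. Nor is either margin judged here on its clinical merits.

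The figures assume equal true risks, 253 analysed patients per arm, an unpooled normal approximation (confirmed by exact calculation) and a 5% that is meant in absolute points. A full protocol or analysis plan that is not shown may state a single margin. The sentence in this article would still need to be brought into line with it.

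**What to change.** The investigators should record, before data are seen, the one margin they agreed, in absolute percentage points. It should be the figure that was agreed, not the one that happens to fit 506.

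- **If it is 6 points:** replace the sentence with a rule that outpatient care is non-inferior if the upper limit of the one-sided 95% confidence interval for the risk difference (outpatient minus inpatient) is below 6 percentage points. Remove the 5%. The sample size and power stand. The cost is one sentence.
- **If it is 5 points:** write the same rule with 5, keep the sample size, and restate the power as about 67% at 8% risk to 82% at 5% risk. The cost is a less favourable power statement. Holding 80% at 8% risk would instead take 730 patients (730/0.99 = 737.4, so about 738 with 1% dropout), a real expansion of a trial that the article describes as already recruiting.

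The chosen figure should also be repeated in the analysis section, so that the reported interval is read against one stated limit.
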